### Recruitment {15}

Potential participants will be recruited from outpatients and inpatients in the cardiovascular department by advertisement, verbal promotion by researchers, hospital posters, and doctor referrals.

## Assignment of interventions: allocation

### Sequence generation {16a}

Eligible participants will be randomized in a 2:1:1 ratio into intervention group 1, intervention group 2, or the control group based on a computer-generated (SAS 9.4 statistical software package PROC PLAN process) random sequence. The randomization sequence will be recorded by staff at the sponsor unit, and the randomized code of the trial drug is the unique identification code of participants. Eligible participants will be randomized in blocks of eight within each site and stratified by site.

### Concealment mechanism {16b}

The allocation sequence will be implemented through sequentially numbered, opaque, sealed envelopes that are concealed until the interventions are assigned to a participant. Participants withdrawn from the trial will retain their randomization number (identification codes) if already given. New subjects must always be allotted a new randomization number.

### Implementation {16c}

During this trial, the statistician will generate the allocation sequence, and the investigators will enrol participants and assign participants to interventions based on information obtained upon opening the randomization number envelope.

## Assignment of interventions: blinding

### Who will be blinded {17a}

To minimize ascertainment bias, all researchers, participants, physicians, drug administrators, dispensing nurses, and statisticians will be blinded to the type of treatment until the study is completed.

### Procedure for unblinding if needed {17b}

Unblinding will be available if participants experience severe adverse events (SAEs) or need to be rescued in an emergency situation. Once unblinded, the participant will withdraw from the study. Researchers should report the reasons to the inspector within 24 h. The precise cause of unblinding, date of adverse events (AEs), treatment situation, and results must be recorded in electronic case record forms (eCRFs).

## Data collection and management

### Plans for assessment and collection of outcomes {18a}

According to the requirements of GCP, the investigator shall fill in data to CRFs accurately, completely, and in a timely manner based on original observations of the subjects. The auditor shall monitor whether all CRFs have been completed correctly and are consistent with the source data and shall pose questions at any time in case of any problem. If errors and omissions are made, the researcher shall be corrected promptly. All data will be stored securely in line with local data management arrangements. Data management will be implemented by Beijing Yilian Zhongkang Technology Co., Ltd.

### Plans to promote participant retention and complete follow-up {18b}

To promote participant retention, at each medicine distribution visit, participants will be scheduled by phone, sent messages, and called the day before. Missed visits will be rescheduled and followed up. The sponsor will provide compensation for transportation costs.

### Data management {19}

CRFs are paper-based. Source data will be collected at each site from the investigator and will be transferred into the CRFs. Source data will be stored in the respective centre. The destruction of any paper files will occur at least 5 years from the termination of the study and will be authorized by the sponsor and the principal investigator.

EpiData Software version 3.1 (the EpiData Association, Odense, Denmark) will be used to store outcome measurement data. Two personnel will undertake double-entry and proofreading independently to ensure the accuracy of the data input from the CRF to EPidata. Electronic data files will be backed up and password protected.

### Confidentiality {27}

Participant identification numbers are used to track data collection documents. Interventionists’ paper documents (CRFs) are stored in a locked file cabinet. The CRFs only use the first letter of the name to identify the participant and do not include the participant’s home address. Access to electronic data is password protected and restricted to the research team. Data exchanged between research sites are deidentified, encrypted, and password protected.

This protocol, CRFs, and other documents and materials related to the trial will be kept strictly confidential and will not be disclosed to third parties unless expressly agreed upon by the principal investigator in advance. Staff of the investigators involved in this trial are also bound by the agreement.

### Plans for collection, laboratory evaluation, and storage of biological specimens for genetic or molecular analysis in this trial/future use {33}

Participants are asked to give explicit consent for blood sample collection and use. For blood sample collection, subjects will be required to fast for 10 h before each collection; 5 mL of blood will be drawn and centrifuged, and the serum will be stored in an Eppendorf tube at − 70 °C.

## Statistical methods

### Statistical methods for primary and secondary outcomes {20a}

The statistical analysis plan will be specified before data analysis. Statistical Analysis System v9.4 (or a higher version) will be used for statistical analysis. Professional statisticians who are independent of all other processes in our study will carry out the analyses.

For continuous variables, we will calculate the mean, standard deviation, median, minimum, maximum, and interquartile range. For categorical variables, we will report various frequencies or percentages. The chi-square test or Fisher’s exact test will be used for categorical variables. For variables with a normal distribution, intergroup comparisons will be analysed with one-way ANOVA, whereas pairwise comparisons before and after treatment will be performed with Student’s *t* test. For data that do not have a normal distribution, intragroup or intergroup differences before and after treatment will be analysed by the Wilcoxon rank-sum test. The proportion of patients with AEs will be compared using the chi-square test or Fisher’s exact test.

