### Outcomes {12}

#### Primary outcome

The primary outcome is the efficacy rate of stable angina symptom score classification [24]. The stable angina symptom score includes the attack frequency, duration, activity level of effort-induced angina pectoris, and pain degree. The indicators of the baseline period (0 weeks) and treatment period (28 days) will be compared.

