**Efficacy indicators**			
Stable angina symptom score		×	×
Electrocardiogram		×	×
Seattle Angina Questionnaire		×	×
Nitroglycerin consumption	×	×	×

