### Sample size {14}

The sample size is calculated using PASS 15 software (NCSS, Kaysville, UT) and driven by the efficacy rate of stable angina symptom score improvement. According to the referenced literature [27, 28], the efficacy rate in relieving stable angina symptoms of NXT is expected to be 85%, 70% for BYHW, and 50% for placebo.

The PASS parameters are as follows: “Proportions>Contingency Table (Chi-Square Tests)>Chi-Square Tests”, “Chi-Square Effect Size Estimator> Contingency Table”. Input the percentage values: placebo = 50%, BYHW = 70%, NXT = “85%”, copy effect size = “0.308210”. Design solve for “sample size”, DF = 2, Power = 0.8, Alpha = 0.05, input effect size = “0.308210”. Then we can get numeric results: *N* = 102, Chi-square = 9.6893, Alpha = 0.05000, Beta = 0.19763. Considering a drop rate of 20%, the dropout-inflated sample size = 128, and expected number of dropouts = 26. According to the ratio of 2:1:1, there will be 64 cases in intervention group 1, 32 cases each in the intervention group 2 and control group. Since this study intends to further compare the NXT and BYHW groups, according to NXT = 85%, BYHW = 70%, W = 0.3082, DF = 1, and the sample size of NXT and BYHW calculated in the previous step, we can reach a power of 0.85540.

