### Methods for additional analyses (e.g. subgroup analyses) {20b}

We will include sex, centre, complications, and concomitant medication as covariates in an analysis of covariance (ANOVA) for significant differences between groups by reducing the error variance.

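### The binary primary endpoint is tested without the baseline symptom score that the trial collects: a valid test, but one that may give up some power

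*Protocol article*

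**What the plan says.** Under Primary outcome: "The primary outcome is the efficacy rate of stable angina symptom score classification". The same section makes it a comparison with baseline: "The indicators of the baseline period (0 weeks) and treatment period (28 days) will be compared". Table 4 (Participant timeline {13}) lists "Stable angina symptom score" among the efficacy indicators and marks it at baseline and in the intervention period.

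Statistical methods {20a} gives the test for every categorical variable: "The chi-square test or Fisher’s exact test will be used for categorical variables". Neither takes a covariate. Sample size {14} uses the same unadjusted test across three groups, with "DF = 2, Power = 0.8, Alpha = 0.05" and these rates: "the efficacy rate in relieving stable angina symptoms of NXT is expected to be 85%, 70% for BYHW, and 50% for placebo".

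Additional analyses {20b} plans one covariate analysis: "We will include sex, centre, complications, and concomitant medication as covariates". It is described as an analysis of covariance meant to reduce error variance. The baseline symptom score is not on its list.

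**The concern.** Eligibility spans grades I to III, so baseline severity will vary. Response is judged against the patient's own starting point, so it may well depend on how severe the symptoms were at the start. If so, an unadjusted test leaves that variation in the error term and cannot correct a chance difference in severity between arms. Randomisation is stratified by site only. The standard error of the chance difference in mean baseline score is √(1/64 + 1/32) = 0.22 SD for NXT against either other arm, and √(1/32 + 1/32) = 0.25 SD for BYHW against placebo.

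Section {20b} accepts adjustment as a way to cut error variance, but pairs it with a model built for continuous outcomes and leaves out the baseline value of the primary measure. At stake is power that could be had without another patient.

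**Working it through.** **1. The plan's own figure.** With equal weights, the mean of 0.50, 0.70 and 0.85 is 0.6833.

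- W² = [(0.1833² + 0.0167² + 0.1667²)/3] / (0.6833 × 0.3167) = 0.02056/0.21639 = 0.0950, so W = 0.3082.
- Noncentrality = 102 × 0.0950 = 9.69. Power with 2 df at 5% is 80.2%, as stated. 102/0.8 gives 128.
- At the actual 2:1:1 allocation the mean is 0.725 and W = √(0.020625/0.199375) = 0.3216. Power is 83.7% at N = 102 and 91.3% at N = 128.

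**2. Rough size of the gain.** If baseline explains a share R² of within-arm response variance, noncentrality becomes 9.69/(1 − R²). From 80.2%, power rises to 82.3% (R² 0.05), 84.5% (0.10), 85.5% (0.125), 88.6% (0.20) or 90.6% (0.25). A 5-point gain therefore needs R² of about 0.11 to 0.13. The protocol gives no R², correlation or odds ratio, so each of these values is an assumption.

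**3. Simulation with a score test.** 6,000 trials per cell; logistic response with a standardised baseline score; marginal rates held at 85/70/50%. Entries are power in %, chi-square → adjusted score test. r is the within-arm correlation at a 70% rate.

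| Odds ratio per SD (r) | 2-df, 51/26/25 | 2-df, 64/32/32 | NXT vs BYHW, 64/32 |
|---|---|---|---|
| 1 (0) | 85.3 → 85.6 | 91.9 → 91.8 | 43.0 → 42.7 |
| 1.5 (0.18) | 84.6 → 86.0 | 91.6 → 92.1 | 42.1 → 42.6 |
| 2 (0.29) | 84.2 → 87.3 | 92.3 → 94.0 | 42.0 → 44.7 |
| 2.5 (0.36) | 84.0 → 88.4 | 91.2 → 94.7 | 44.0 → 46.9 |
| 3 (0.41) | 84.7 → 90.6 | 91.1 → 95.3 | 43.1 → 48.3 |
| 4 (0.48) | 83.8 → 92.2 | 91.0 → 96.8 | 42.8 → 49.8 |

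**4. The same on a latent scale.** Here each patient has a normal response propensity correlated ρ with baseline, cut to give the plan's rates. The observed r at a 70% rate is ρ × 0.348/√0.21 = 0.76ρ, so ρ of 0.3, 0.5 and 0.6 correspond to r of 0.23, 0.38 and 0.46. Score-test gains on the 2-df test (2,500 trials per cell) are:

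- 51/26/25: about 0, 2, 6 and 8 points at ρ = 0, 0.3, 0.5 and 0.6.
- 64/32/32: about 0, 1, 3 and 4 points.

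A repeat with 10,000 trials per cell agreed within about a point: 0, 2, 6 and 8; then 0, 1, 3 and just under 5. In that repeat NXT versus BYHW at ρ = 0.6 rose from 34% to 42% with 51/26, and from 43% to just under 50% with 64/32.

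**5. Test size.** Under the null the score test rejected in 4.5 to 5.7% of trials. The logistic likelihood-ratio test rejected in up to about 6%, so part of any gain quoted for it is inflated size.

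**The case against.** The strongest reply is that nothing here is wrong. The chi-square test holds its level, is the test the trial was sized on and matches the stated metric, a difference in proportions. That stands, and it rules out calling this an error or a bias.

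Second, covariates are often left to the analysis plan, which is not shown. This carries less weight, because the article does not stay silent: it names the test and a covariate list, and the list omits this score.

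Third, response is already relative to baseline and the classification rule sits in a cited source. If the rule is a proportional reduction, baseline may be largely normalised out. This also stands. The strength and even the direction of the relation are unknown, so zero belongs in the range.

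Fourth, assuming 20% of patients lost overstates the gain. The full analysis set takes everyone randomised who received a dose, with last observation carried forward, which comes close to 64/32/32. There the three-group gain is roughly half as large.

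A reader might infer a firm loss of about 5 points. The documents fix no such figure; it depends on an assumed correlation near 0.5 and on 51/26/25 evaluable. A reader might also infer that adjustment rescues NXT versus BYHW. It does not: that contrast stays below 50% power. The stated 0.85540 for it comes from reusing the three-group W of 0.3082; the actual W for 85% against 70% at 64/32 is 0.177, with power near 41%. That is a separate and larger problem.

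**Conclusion.** The point holds as one of efficiency. The plan picks a valid unadjusted test, collects the baseline score and omits it from its only covariate analysis. For latent correlations between 0 and 0.6, the three-group test would gain about 0 to 8 points with 51/26/25 evaluable and about 0 to 4 or 5 points with 64/32/32 analysed. NXT versus BYHW would gain about 0 to 8 points and remain below 50%.

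These ranges rest on the plan's 85/70/50% rates, on a monotone relation between baseline score and response, and on correlations that the protocol does not supply. The change is worth making because it is nearly free, not because the planned test would mislead.

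**What to change.** In {20a}, make the primary test a logistic regression of effective / not effective on treatment arm with the continuous baseline symptom score as covariate. Take the p-value from a score test, or from a re-randomisation test that redraws the 2:1:1 sequence in blocks of eight within site, so that the 5% level holds. Report standardised (marginal) risk differences for the pairwise comparisons, so the result is still a difference in efficacy rates. Keep the chi-square test as a supporting analysis. In {20b}, confine the analysis of covariance to continuous outcomes.

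This needs no new data and no extra patients. The article says that the analysis plan is still to be specified and that no analysis has been done, so the choice could still be made in advance. The cost is one sentence of wording and reliance on a simple model. With the score test, power changes by about 1 point or less if baseline turns out not to predict response.

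### Randomisation is stratified by site, but the tests named for the binary primary outcome ignore site; if response rates differ between sites, the pooled test is conservative and forgoes some power

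*Protocol article*

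**What the plan says.** Three sections of the protocol article bear on this.

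- Sequence generation {16a}: "Eligible participants will be randomized in blocks of eight within each site and stratified by site". Study setting {9} lists six sites, and allocation is 2:1:1.
- Statistical methods for primary and secondary outcomes {20a}: "The chi-square test or Fisher’s exact test will be used for categorical variables". The primary outcome is an efficacy rate, which Table 3 summarises as a proportion, so this sentence governs it. No site term or stratified test is named.
- Methods for additional analyses {20b}: "We will include sex, centre, complications, and concomitant medication as covariates". The model named there is an analysis of covariance, abbreviated as ANOVA.

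Sample size {14} uses the same kind of test as {20a}. The PASS menu path is "Proportions>Contingency Table (Chi-Square Tests)>Chi-Square Tests", with no allowance for site.

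**The concern.** Blocking within site keeps the arms balanced inside each hospital, so differences in response between hospitals largely cancel out of the comparison of arms. The pooled chi-square test does not know this. Its variance is built on the overall proportion, and for site-specific rates p_s

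p̄(1 − p̄) = mean of p_s(1 − p_s) + variance of p_s.

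Only the first term contributes to the real sampling variation of the difference between arms when allocation is balanced by site. If the p_s differ, the second term makes the variance too large. The actual type I error then falls below 5%, and power that the design has already provided is left unused.

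The additional analysis does not clearly repair this. An analysis of covariance is a model for continuous outcomes, and the article names no site-adjusted model that fits a binary one.

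**Working it through.** **1. Reproduce the plan's figure.** The inputs come from Sample size {14}: "the efficacy rate in relieving stable angina symptoms of NXT is expected to be 85%, 70% for BYHW, and 50% for placebo", with "DF = 2, Power = 0.8, Alpha = 0.05".

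- With equal group weights, p̄ = (0.50 + 0.70 + 0.85)/3 = 0.6833.
- W² = [(0.1833² + 0.0167² + 0.1667²)/3] / (0.6833 × 0.3167) = 0.02056/0.2164 = 0.0950, so W = 0.30821.
- Non-centrality at N = 102 is 102 × 0.30821² = 9.6893. Power from the non-central chi-square with 2 df is 0.80237.
- The article gives "Chi-square = 9.6893, Alpha = 0.05000, Beta = 0.19763", which matches.
- 102/0.8 = 127.5, rounded up to 128, which also matches.

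The stated power was therefore computed for an unstratified test.

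**2. Compare the pooled and stratified tests.** The setting was:

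- N = 128 at 2:1:1, with six sites of 24, 24, 24, 24, 16 and 16 (complete blocks of eight).
- Site effects normal on the logit scale, with overall rates held at 85%, 70% and 50% (70% in every arm under the null).
- 40,000 simulated trials per scenario. The Monte Carlo standard error is about 0.001 for type I error and 0.0015 for three-arm power.

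For two arms, the Cochran-Mantel-Haenszel (CMH) statistic is

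[Σ_s (a_s − m_s n_1s/n_s)]² / Σ_s [m_s(n_s − m_s) n_1s n_2s / (n_s²(n_s − 1))],

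where a_s is the number of responders in arm 1 at site s, m_s all responders there, and n_1s, n_2s and n_s the arm and site sizes. For three arms the general-association form with 2 df was used.

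The site SD is an assumption. The second column shows what it means: response at sites one SD either side of a 50% site.

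NXT versus BYHW, 64 versus 32:

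| Site SD | Site rates | Type I error, pooled / CMH | Power, pooled / CMH | Gain (points) |
|---|---|---|---|---|
| 0 | 50% | 0.050 / 0.049 | 0.430 / 0.422 | −0.8 |
| 0.5 | 38–62% | 0.047 / 0.050 | 0.423 / 0.425 | 0.1 |
| 1.0 | 27–73% | 0.035 / 0.048 | 0.430 / 0.460 | 3.0 |
| 1.5 | 18–82% | 0.026 / 0.048 | 0.429 / 0.502 | 7.3 |

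Three arms, N = 128:

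| Site SD | Type I error, pooled / CMH | Power, pooled / CMH | Gain (points) |
|---|---|---|---|
| 0 | 0.052 / 0.049 | 0.917 / 0.914 | −0.3 |
| 0.5 | 0.044 / 0.048 | 0.921 / 0.926 | 0.5 |
| 1.0 | 0.034 / 0.051 | 0.924 / 0.945 | 2.1 |
| 1.5 | 0.024 / 0.049 | 0.922 / 0.964 | 4.2 |

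At N = 104, close to the evaluable number, the three-arm gains at SD 0.5, 1.0 and 1.5 are 0.8, 3.4 and 6.7 points.

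Separate simulations of the two-arm comparison gave pooled type I errors of 4.4–4.5%, 3.5–3.7% and 2.6–2.7% at SD 0.5, 1.0 and 1.5. Incomplete blocks and dropout patterns were not simulated.

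The pairwise power near 0.42 is far below the 0.85540 in Sample size {14}, but not because of site. That figure reuses the three-group W of 0.3082. For 85% versus 70% at 2:1, p̄ = 0.80 and W² = [(2/3)(0.05²) + (1/3)(0.10²)]/0.16 = 0.03125, so W = 0.177. This is a separate matter, and stratifying does not cure it.

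**The case against.** The strongest reply is that no harm is shown. The documents report no between-site variation. At nil to moderate variation the two tests differ by less than 1 point of power, and a gain of 3 points or more for NXT versus BYHW needs an SD of about 1.0, which is a wide spread of site rates. A symptom score rated at six hospitals may differ by site, but a reader who infers that it will differ goes beyond the text. This part of the reply stands, and the point has to be put conditionally.

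A reader might also infer that the trial is less powerful than planned. It is not. The trial was sized with the same unstratified test, and the pooled test's own power stays flat as site variation grows (0.917 to 0.925 for three arms). What is forgone is a possible gain.

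A reader might add the known conservatism of Fisher's test: by exact calculation, power for 85% versus 70% at 64 versus 32 is 35.9%, against 42.4% for chi-square. That loss has nothing to do with site, and the fallback is unlikely to be needed at the planned rates. The smallest expected count is 32 × 19.2/96 = 6.4 for the pair and 32 × 35.2/128 = 8.8 for three arms, both above the usual threshold of 5.

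Finally, the article promises an analysis plan, and the covariate sentence names no outcome, so it may be meant for continuous measures such as the Seattle Angina Questionnaire. That is fair, and the sentence does not prove that site will be ignored. But the article does not merely leave the matter open: it names an unstratified test for categorical outcomes, and its only route for centre is a model that does not fit its primary outcome.

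**Conclusion.** The mismatch is real and modest. The trial randomises by site, and the tests named for its binary primary outcome do not use site. If response rates differ between sites, the pooled test is conservative, with type I error of about 4.5%, 3.5% and 2.6% at an assumed site SD of 0.5, 1.0 and 1.5. A stratified test would then recover about 0, 3 and 7 points of power for NXT versus BYHW, and about 0.5, 2 and 4 points for three arms at N = 128.

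These sizes rest on the assumed SDs, logit-normal site effects, complete blocks and full recruitment without dropout. The error runs only in the safe direction: false positives are not inflated, the stated three-arm power is not eroded, and no conclusion of the trial would be invalidated. It is an efficiency point worth acting on because the change is cheap and NXT versus BYHW, the second stated objective, has little power to spare.

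**What to change.** In {20a}, and in the analysis plan it promises:

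- Make the primary test a Cochran-Mantel-Haenszel test stratified by site: three-arm general association first, then the pairwise comparisons.
- Report the Mantel-Haenszel risk difference with a 95% CI for each pair.
- Pre-specify a rule for pooling very small sites, for example those recruiting less than one full block of eight.

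In {20b}, replace the analysis of covariance, for the binary outcome, with logistic regression on arm and site.

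The cost is a change of wording, plus under 1 point of power if sites turn out not to differ. Trial status reports that recruitment is in progress and no analysis has been done, so on that account the change can still be pre-specified.

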### Objectives {7}

The objectives of this study were (i) to evaluate the efficacy of NXT and BYHW in the treatment of SAP and (ii) to test whether NXT is more advantageous than BYHW for treating SAP.

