### Interventions

#### Explanation for the choice of comparators {6b}

Given the complexity of SAP and the urgent need for evidence-based therapy approaches, we chose to add TCM on the basis of standardized treatments and compare the efficacy of NXT and BYHW in relieving stable angina symptoms (including the frequency of angina attacks, duration and degree of pain).

The two intervention groups, i.e. the NXT group and BYHW group, will be compared to the placebo group to evaluate the efficacy of NXT and BYHW in the treatment of SAP. Furthermore, the NXT group will be compared to the BYHW group to evaluate whether NXT is more advantageous than BYHW for treating SAP.

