***Secondary outcomes***				
ECG parameters	Classification of 12-lead ECG improvement [23]	Difference between two groups	Proportion	Baseline, 28 days after treatment
SAQ scores	SAQ [24]	Difference in the change between groups	Mean/ median	Baseline, 28 days after treatment
Nitroglycerin consumption	Count	Compare the difference between groups	Median	Baseline, 28 days after treatment

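### For the continuous outcomes, before-after significance tests inside each arm do not answer the trial's between-arm questions and, with 2:1:1 arms, tilt chance discordance towards NXT

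*Protocol article*

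**What the plan says.** Under Statistical methods for primary and secondary outcomes {20a}, the protocol article states that for normally distributed variables "intergroup comparisons will be analysed with one-way ANOVA", and then, as a contrast, that "pairwise comparisons before and after treatment will be performed with Student’s" t test. For other distributions, "intragroup or intergroup differences before and after treatment will be analysed by the Wilcoxon rank-sum test". Nothing labels the within-arm tests as descriptive.

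The questions are set elsewhere. Objectives {7} includes "to test whether NXT is more advantageous than BYHW for treating SAP". The section on the choice of comparators {6b} sets each drug against placebo and adds that "the NXT group will be compared to the BYHW group to evaluate whether NXT is more advantageous than BYHW for treating SAP". Table 3 gives the SAQ metric as "Difference in the change between groups".

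The primary outcome is a proportion. Table 3 gives its metric as a difference between groups, and {20a} says "The chi-square test or Fisher’s exact test will be used for categorical variables".

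**The concern.** The null hypothesis of a before-after test is that nothing changed over four weeks. An arm can violate it through background treatment, placebo response, natural course or regression to the mean. The sample size section itself expects 50% of placebo patients to count as effective, so some improvement without active drug is part of the plan's own assumptions. A significant within-arm result is therefore not evidence that the drug works.

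Two features make this more than a matter of style here. First, for normally distributed outcomes the only intergroup test that {20a} names is an omnibus ANOVA over three groups, which does not say which arms differ. The before-after p-values are then the only clearly arm-specific ones in that section. Second, the 2:1:1 allocation gives the NXT test more power than the BYHW test at the same true change. If readers or authors set the two within-arm results side by side, the imbalance favours the product that the protocol expects to do better.

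This is separate from whether a rank-sum test suits paired data. A correctly paired test has the same limitation.

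**Working it through.** **Inputs from the sample size section.** 102 patients are needed. With 20% dropout, 102/0.8 = 127.5, so 128, which reproduces the plan's figure. The split is 64/32/32. Completers: 64 × 0.8 = 51.2, about 51; 32 × 0.8 = 25.6, about 26. Two-sided alpha is 0.05.

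**Assumed input.** The article gives no mean change or SD for any continuous outcome. Let d be the true mean change divided by the SD of the change, equal in both drug arms. It is varied from 0.2 to 0.8.

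**Formulas.** The power of a paired t test to show significant improvement is power(n, d) = P(T > t(0.975, n−1)), where T is noncentral t with n−1 degrees of freedom and noncentrality d√n. The arms are independent, so:

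- P(NXT only) = power(NXT) × [1 − power(BYHW)]
- P(BYHW only) = power(BYHW) × [1 − power(NXT)]

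**Worked case, d = 0.4.** NXT: noncentrality 0.4 × √51 = 2.857, power 0.800. BYHW: 0.4 × √26 = 2.040, power 0.500. NXT only = 0.800 × 0.500 = 40%. BYHW only = 0.500 × 0.200 = 10%.

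| d | power, n = 51 | power, n = 26 | NXT only | BYHW only | NXT only, 64 vs 32 |
|---|---|---|---|---|---|
| 0.2 | 0.288 | 0.164 | 24% | 12% | 28% |
| 0.3 | 0.556 | 0.312 | 38% | 14% | 41% |
| 0.4 | 0.800 | 0.500 | 40% | 10% | 36% |
| 0.5 | 0.938 | 0.688 | 29% | 4% | 21% |
| 0.6 | 0.987 | 0.836 | 16% | 1% | 9% |
| 0.7 | 0.998 | 0.929 | 7% | 0.2% | 3% |
| 0.8 | 1.000 | 0.975 | 2.5% | about 0% | 0.8% |

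The last column uses all randomised patients. It is relevant because the plan carries the last observation forward in the full analysis set.

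**Placebo.** The control arm also has about 26 completers. If it changed by the same d, its own before-after test would be significant in 31% of trials at d = 0.3 and 84% at d = 0.6.

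**How much is due to allocation.** With equal arms of the same total (39 and 38), one drug alone is significant in 24 to 25% of trials at d = 0.3 and 21 to 22% at d = 0.4, depending on which arm has the extra patient. The unequal arms give 38% and 40% for NXT alone. Discordance in either direction moves less: from 49% to 52% at d = 0.3 and from 44% to 50% at d = 0.4. In that range allocation mainly shifts the direction.

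**Direct comparison.** A two-sample t test on change, simulated with 64 versus 32 and 40,000 trials at each of several values of d, rejects in about 5% of trials when the drugs are equal and favours NXT in about 2.5%, whatever d is.

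**The case against.** The strongest reply is that between-arm tests are already planned and the within-arm tests only accompany them. That is right. The comparator section and Table 3 point to between-group contrasts, and the additional-analyses section adds a covariance analysis between groups. A reader might infer that the NXT versus BYHW conclusion will be drawn from one arm being significant and the other not. No passage says so; the harm needs a misreading that the plan leaves open but does not prescribe.

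A reader might also think the primary result is exposed, citing the Primary outcome section: "The indicators of the baseline period (0 weeks) and treatment period (28 days) will be compared". That sentence most naturally says how each patient's response is derived from baseline. The efficacy rate is a proportion compared between groups, and the sample size rests on a between-group chi-square test. The primary outcome is outside this point.

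Third, the wording of the t-test sentence could mean pairs of groups. The explicit mention of intragroup differences in the next sentence supports the within-arm reading.

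Finally, labelling supplementary tests is often left to the analysis plan. Even so, the article states these tests as part of the methods for primary and secondary outcomes without any such label, so the choice is made here.

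**Conclusion.** The point holds for the continuous outcomes, mainly SAQ. The plan includes within-arm hypothesis tests whose null is not a trial question, and for normally distributed data they supply the only clearly arm-specific p-values in {20a}.

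The size depends on an unknown. Over 0.2 to 0.5 SD of common change, chance discordance favours NXT by a clear margin. From about 0.7 SD upwards it is uncommon: both drug arms are usually significant, and the tests say nothing about the drugs. It would therefore be too strong to say that equal drugs would often look different, or that the discordance comes mainly from the allocation; at 0.3 and 0.4 SD more than half of the NXT-only figure would occur with equal arms. The calculation also assumes normal changes with a common SD and about 20% dropout in each arm.

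This is a modest point, worth correcting because it costs almost nothing and recruitment was still in progress with no analysis done.

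**What to change.** In Statistical methods for primary and secondary outcomes {20a}:

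- Replace the within-arm before-after tests with descriptive reporting: mean or median change in each arm with its 95% confidence interval and no hypothesis test.
- State that conclusions on continuous outcomes rest on between-arm differences in change, with 95% confidence intervals, for NXT versus placebo, BYHW versus placebo and NXT versus BYHW.

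Leave the baseline-to-day-28 sentence under Primary outcome as it is, since it describes how response is derived.

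The change is a few lines of wording and needs no new data or patients. The loss is a set of within-arm p-values that some readers expect.
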